## Abstract

**Background:**

Patients with heart disease often suffer from difficulties in psychological adaptation during cardiac rehabilitation. Mood disorders such as depression are known to be highly prevalent in cardiac patients and to have a negative impact on the progression of coronary heart disease. However, cardiac patients have difficulties to get psychological treatments due to low availability and motivational difficulties. Web-based interventions have been proven to be effective in treating depressive symptoms. Deprexis is a promising web-based psychological treatment which was devised for depressed patients. The aim of the study InterHerz is to examine if Deprexis is an effective psychological treatment to reduce stress and depression in cardiac patients.

**Methods/Design:**

The sample will consist of 80 depressed patients randomized to an intervention group or a waitlist (10 weeks). Patients are recruited via cardiologists, cardiac rehabilitation units and the website of the Swiss Heart Foundation. Patients have access to a guided self-help program in which they work themselves through several modules and receive feedback from a clinical psychologist. Pre- and post-assessments, and a six-month follow-up, are conducted using online questionnaires and diagnostic interviews.

**Discussion:**

Deprexis is a new web-based treatment which has the potential to help depressed cardiac patients with limited access to psychological treatment to increase their mental health.

**Trial registration:**

Current Controlled Trials ISRCTN45945396

## Background

There is a large body of evidence that high or prolonged stress, depression and low social support are predictive of coronary artery health [1-4]. In particular, depression has been identified as a psychosocial factor with enormous potential to influence the course and outcome of coronary artery disease [3,5,6]. Despite the empirical evidence that depression increases the risk of cardiovascular morbidity and mortality itself, there is no common accepted model that describes the underlying mechanisms [7,8]. Both direct and indirect pathways have been put forward. On one hand, direct influences of depression on physiological factors may lead to atherosclerosis or coronary events. On the other hand, depression leads to an increase in coronary risk factors (that is, inflammation), which in turn may cause heart disease. Finally, there may be some underlying factors (that is, distress, personality, social environment and health behavior) influencing the risk for both depression and heart disease [9]. Psychosocial and behavioral factors correlate both with depression and heart disease. Depression is associated with poor health behavior, maladaptive coping style, social isolation, and chronic life stress [10]. Behavioral risk factors, such as smoking, low physical activity, a poor diet, and the failure to adhere to medical recommendations mediate the relationship of depressive disorders with heart disease [11,12].

Several studies have focused on the treatment of depressive symptoms in cardiac patients. The study, enhancing recovery in coronary heart disease patients with depres-sion (ENRICHD), examined the efficacy of psychotherapy (cognitive-behavioral approach) on depression [13]. The effect size (ES) of short-term efficacy in comparison to the control group were small (ES = 0.35), and disappeared on long-term follow-up. Furthermore, the Canadian cardiac randomized evaluation of antidepressant and psychotherapy efficacy (CREATE) study, investigating the benefit of an interpersonal psychotherapy (IPT) [14], only detected a tendency towards a reduced depression level in the IPT group compared to the non-treated group (ES = 0.20). Larger ES over 0.70 were reported for psychotherapy in depressed but otherwise healthy people. However, these effects might be overestimated due to publication bias [15].

One of the greatest challenges of a psychotherapeutic approach to support treatment success of cardiac patients with depression is the time and resource intensity of most traditional approaches of treatment delivery. The opportunity to develop new forms of intervention, for example, web-based treatment, has never been more feasible. To date, there is sparse evidence that psychotherapy influences the progress of heart disease.

Many people are now web-literate and many have access to the Internet. Today, internet-based technologies are used at almost all levels of psychosocial services. Apart from possible cost-effectiveness and the fact that web-based interventions can flexibly be used independently of time and place, a major advantage of the web-based approach is that it offers support to people who may not otherwise seek or reach treatment.

Over recent years, web-based treatments have been used with success to promote health [16,17] and have shown promising outcomes for several psychiatric conditions, including depression [18-20]. Particularly web-based guided self-help approaches, in which the presentation of a web-based self-help program is combined with minimal but regular therapist contact via e-mail, have shown promising results. Emerging evidence from meta-analyses [19,21] and from a reanalysis of data across trials [22] suggests a superiority of guided versus unguided self-help, both in terms of efficacy and drop-out rates.

There are only a few web-based interventions for cardiac patients that have been developed and evaluated so far [23]. Preliminary results confirm that a web-based intervention for cardiac patients can help to change psychosocial risk factors. Web-based interventions can reduce symptoms of depression [24,25] and anxiety [25,26] and help to increase social support [27]. Besides this, cardiac patients report improvements in managing their physical condition by knowing more about their disease, and therefore increase their perception of control [28] and change their health behavior [29,30]. In addition, improvements in quality of life [27,31,32], and even improvements in adherence due to the presentation of a cardiac-specific information tool [25,33] have been reported.

There are only two web-based psychological treatment programs to have been developed so far: a specific web-based distress management program for patients with cardioverter defibrillator [34] and a web-based treatment for cardiac patients with depression [35].

In consideration of the difficulties of treating cardiac patients, this intervention study InterHerz strikes a new path by implementing a proven and promising web-based approach called Deprexis in a somatically ill patient group with depression [36-38]. Deprexis has been developed to reduce depressive symptoms in physically healthy patients with a depressive disorder. To our knowledge, this is the only psychological treatment for German-speaking patients with depression, and in contrast to other web-based tools, it integrates different psychotherapeutic approaches [36].

## Methods/Design

### Aims

The primary aim of InterHerz is to investigate whether the proven web-based treatment Deprexis is effective to reduce depression and perceived stress in cardiac patients. Secondary aims are to examine the mid-term effects of Deprexis on depression, perception of stress, social support, and changes in health behavior after six months follow-up.

### Design

The study uses a randomized controlled design comparing a web-based treatment with a waitlist control condition. All patients in the treatment group receive basic information on the use of the program, a booklet on depression and heart disease, a personal user name and a password. They have immediate access to the program. Patients under the waitlist condition receive the equivalent access to the program after a waiting period of 10 weeks. The randomization sequence is generated by the website Research Randomizer ([http://www.randomizer.org]) and concealed in the study center of the Institute for Social and Preventive Medicine, University of Bern (Switzerland).

### Sample size calculation

In a previous study testing the same psychological treatment in depressed patients, medium to large between-group effect sizes were found [37]. Assuming medium between-group effects, 80 randomized patients in total (40 patients per treatment condition) are needed in this study. This estimation is based on the assumptions of a level of significance of 0.05 (two-sided), 80% statistical power (1-Beta), and correlations between pre- and post-assessment found in previous studies, and the estimate was calculated using G-Power [39].

### Study sample

Patients with any coronary artery disease are invited to participate in the study. We estimate a number of more than 2,000 patients who shall be reached through the collaborating cardiology institutions (for example, rehabilitation centers, hospitals). The Swiss Heart Foundation and the Swiss Association of Cardiovascular Prevention and Rehabilitation support the project through advertisement of the InterHerz study on their website and through the distribution of flyers. Assuming more than 2,000 patients will be informed about our web-based intervention, we expect about 300 patients to show initial interest via email. According to our earlier research on web-based interventions, about half of the patients who initially show interest and contact us will give their written consent and fill out the screening questionnaires (n = 150). After a clinical interview and the application of inclusion criteria we expect a total number of 80 patients to be randomized to the two treatment conditions (for details see the flow chart in Figure 1).

**Figure 1 F1:**
[figure not shown]
Recruitment and participant flow.

### Inclusion and exclusion criteria

Adults who suffer from any cardiovascular disorder (including coronary heart disease, chronic heart failure, and arrhythmias) can apply to participate. Patients are included if they return the informed consent, are 18 years or older, have symptoms of depression (as defined by scoring above a cut-off of 9 on the Beck Depression Inventory (BDI-II)), are of sufficient knowledge of German language, and have access to the Internet. If patients have any acute health threatening disease (for example, cancer), a severe psychiatric illness (for example, psychosis, dementia), suicidal thoughts or plans, or an unstable heart condition, they are excluded from the study. Participants will remain in the study in case of further progression of heart disease during study participation.

### Intervention

The intervention is a web-based psychological treatment called Deprexis, which has been evaluated in previous trials [8] (http://www.deprexis.de). Deprexis was developed to reduce depressive symptoms in patients who do not have any somatic disease. The treatment consists of 10 content modules. All modules can each be completed in 10 to 60 minutes, depending on the user’s reading speed, interest, motivation, and individual path through the program. The modules are organized as simulated dialogues in which the program explains and illustrates concepts and techniques, engages the user in exercises, and continuously asks users to respond by selecting from response options. Subsequent content is then tailored to the users’ responses, resulting in a simulated conversational flow. The modules cover a variety of therapeutic content that is broadly consistent with a cognitive-behavioral perspective, although the program is not restricted to one cognitive behavioral therapy (CBT) manual. Instead, an effort was made to design the program as an integrative treatment tool that provides a variety of relevant therapeutic approaches and fits within the broad array of contemporary CBT (see Table 1). The link to the website of the InterHerz study is provided from the applicant’s institution (https://www.online-therapy.ch/interherz).

**Table 1 T1:** Components included in the psychological treatment Deprexis

**Number**	**Component**
1	Behavioral activation
2	Cognitive modification
3	Mindfulness and acceptance
4	Interpersonal skills
5	Relaxation, physical exercise and lifestyle modification
6	Problem solving
7	Childhood experiences and early schemas
8	Positive psychology interventions
9	Dreamwork and emotion-focused interventions
10	Psychoeducation

During their work through Deprexis, participants are guided by a clinical psychologist. Weekly feedback on patient’s work and progress are given via an integrated email system. Participants are able to contact the psychologist via email if they have any questions during the intervention period.

### Assessment

The efficacy of the intervention is assessed post-treatment (T2) and additionally at 6 months follow-up (T3). Pre-treatment assessment (T0) is conducted by a psychologist before the randomization procedure to assess the level of depression, and to collect information on perceived stress, perceived social support and quality of life. At baseline, we further assess medical information on the disease, duration of the disease, time of the event, risk behavior (for example, smoking, low physical activity, poor diet), and medication or other psychotherapeutic treatments. Moreover, a clinical diagnostic interview is conducted by phone. To address the research question, depression levels are measured during treatment (T1), and treatment satisfaction is measured at the end of the treatment (T2).

### Measures

The German version of the Beck Depression Inventory (BDI-II) [40] is administered to assess the level of depressive symptoms. Ten points or more is to be considered a clinically relevant score for depressive symptomatology. All patients with depressive symptoms above this cut off are asked to fill out the German version of the Patient Health Questionnaire (PHQ-D) [41] and are additionally interviewed by a psychologist with the Structured Clinical Interview for DSM diagnosis (SCID) to classify patients as clinically depressed according to the American Psychiatric Association Diagnostic and Statistical Manual [42]. Stress perception is assessed by the Perceived Stress Questionnaire PSQ [43] and perceived social support by the German version of the self-rated 7-item ENRICHD Social Support Inventory (ESSI) [44]. The World Health Organization (WHO) quality of life-BREF (WHOQOL-BREF) (German version) [45], a brief form of a transcultural quality of life assessment instrument developed by the WHO, is used to measure quality of life. Client satisfaction is assessed post-treatment with the German version of the Client Satisfaction Questionnaire (CSQ) [46]. Medication and compliance with medication are assessed by free text and health-related lifestyle (for example smoking, physical activity, diet) with dichotomous items in line with earlier studies by the research team [47].

### Ethics considerations

The study protocol was approved by the Local Ethical Committee of the Faculty of Human Sciences, University of Bern and is in accordance with the Declaration of Helsinki. All patients receive written information about the aim of the study, benefits and risks of participation and the exact study procedure before giving their written informed consent to participate in the study. At that time all participants are informed that they can cancel participation without disclosing any reason at any time during the study.

With each participant an individual emergency plan is developed at the beginning of the study via a personal call. They receive information on nearby facilities in case of an emotional crisis (crisis intervention ward, psychiatric emergency units). In addition, an emergency link on the homepage provides telephone numbers and several addresses of treatment institutions that can be contacted 24 h a day. Patients with a suicidal tendency are excluded from the study. They are informed that a web-based intervention is not an appropriate treatment for patients in emotional crisis and are asked to seek help within a face-to-face setting. We assist patients in search of these settings.

### Statistical analyses

We will analyse the longitudinal data according to a completer analysis (after the intervention) and in addition we will use intent-to-treat analysis including patients who drop out during the intervention or waiting period. The efficacy of the intervention will be estimated using analysis of variance with baseline values as covariates and additional assessments conducted after 5 sessions (midterm) and after 10 sessions (post). The primary endpoint will be depressive symptoms measured by BDI II and a diagnostic interview after 10 weeks. Secondary end points will be perception of stress, social support, quality of life and compliance. Long-term stability of the efficacy of the intervention will be analysed by comparisons of pre-treatment and follow-up assessments of depression in all participants (InterHerz and waitlist control group) using the *t*-test of dependent samples, and pre-treatment to follow-up effect sizes will be calculated. For the prediction of treatment success we will use clinical variables (for example, severity of cardiac disease), sociodemographic variables (for example, age, gender) and process measures (for example, working alliance). Since missing values are a critical issue in longitudinal studies we will use a statistical algorithm for the estimation of missing values as implemented in SPSS.

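### Completers are analysed first and intent-to-treat is an addition; neither is declared to decide the 10-week primary endpoint, so the headline may come from a group selected after randomisation

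*Protocol article*

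**What the plan says.** The Statistical analyses section of the protocol article opens with the populations: "We will analyse the longitudinal data according to a completer analysis (after the intervention) and in addition we will use intent-to-treat analysis". The second of these is described as "in addition we will use intent-to-treat analysis including patients who drop out during the intervention or waiting period".

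The sentences that follow name no population:
- Model: "The efficacy of the intervention will be estimated using analysis of variance with baseline values as covariates".
- Endpoint: "The primary endpoint will be depressive symptoms measured by BDI II and a diagnostic interview after 10 weeks".
- Missing data: "we will use a statistical algorithm for the estimation of missing values as implemented in SPSS".

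No other section reverses the order, attaches the word primary to either population, or says which result governs if they differ. The Sample size calculation section counts randomised patients: "80 randomized patients in total (40 patients per treatment condition) are needed in this study". It states no allowance for dropout.

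**The concern.** Whether a patient completes is settled after randomisation, and the two arms face different tasks. The Intervention section gives the treated arm ten modules of 10 to 60 minutes with weekly feedback. The Design section has the waitlist wait ten weeks and then receive the program. A patient who is not improving may give up the modules, while a waitlist patient can stay simply by waiting for access. If that happens, the treated completers are a better-off subset, compared with a nearly complete control group, and the comparison is no longer protected by randomisation.

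Two analyses of one endpoint with no deciding rule add a second problem. If they diverge, the text allows the completer result to be the headline, and its wording leans that way.

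**Working it through.** **1. Is there a figure in the plan to reproduce?** Not on this point. The article gives no dropout rate, no dropout difference between arms and no numerical pre-post correlation. It does give 40 patients per arm and a two-sided 5% level, so the nominal chance of a false positive in favour of Deprexis is 2.5%.

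**2. Bias of the completer analysis when there is no true effect.** Assumed: pre-post correlation r = 0.6, so post = 0.6 × baseline + 0.8 × residual, since √(1 − 0.6²) = 0.8. Within each arm a fixed fraction drops out, and the log-odds of leaving rise by a given slope per residual SD of worse outcome. Post is then regressed on baseline and arm in those who remain (4,000 to 6,000 replicates). Bias is in SDs of the outcome, in favour of Deprexis.

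| Dropout, treated / waitlist | Slope | Bias (SD) | False positives in favour |
|---|---|---|---|
| 25% / 5% | 0 (unrelated to outcome) | 0 | nominal |
| 25% / 25% | 1–2 | about 0 | about 3% |
| 15% / 10% or 20% / 15% | 1–2 | 0.03–0.05 | 4–6% |
| 15% / 5% | 1–2 | 0.07–0.10 | 6–9% |
| 25% / 5% | 0.5 | 0.08 | 6% |
| 25% / 5% | 1 | 0.13 | 11% |
| 25% / 5% | 2 | 0.19 | 19% |

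Hand check of the 25% / 5% rows: 30 and 38 patients remain, so SE ≈ 0.8 × √(1/30 + 1/38) = 0.195.
- Slope 1: 0.133/0.195 = 0.68, and the normal tail beyond 1.96 − 0.68 = 1.28 is 10%, close to the simulated 10.8%.
- Slope 2: 0.188/0.195 = 0.96, and the tail beyond 1.00 is 16%. The simulated 19% is higher because selection also narrows the spread among treated completers.

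**3. A second selection model.** Dropout p occurs in the treated arm only, with correlation c between the tendency to leave and a worse outcome, and no baseline adjustment. Then bias = c × φ(z)/(1 − p), with z = Φ⁻¹(1 − p).
- p = 0.20: z = 0.842, φ(z) = 0.280, and 0.280/0.80 = 0.350. Bias is 0.07 SD at c = 0.2 and 0.175 SD at c = 0.5. The two-sided type I error is 6.0% to 11.8%.
- p = 0.30: z = 0.524, φ(z) = 0.348, and 0.348/0.70 = 0.497. Bias is 0.10 to 0.25 SD. The two-sided type I error is 6.9% to 18.1%.

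**4. With a true effect the two analyses answer different questions.** If the effect is 0.50 SD in the 75% of treated patients who continue and zero in the 25% who stop, the intent-to-treat effect is 0.75 × 0.50 + 0.25 × 0 = 0.375 SD. The completer figure is 0.50 SD. This presumes outcomes are observed on those who stop.

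**5. Does relabelling suffice?** No. In step 2 patients leave because of the part of the outcome that baseline does not predict. Filling missing post-treatment scores from a regression on baseline and arm fitted in completers puts every imputed value on the completer line and returns the same arm difference. The planned mid-treatment depression measure might recover part of the loss. Only collecting the outcome from those who stop avoids relying on that.

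**The case against.** The strongest reply is that the article never calls the completer analysis primary. The phrase introducing intent-to-treat can mean simply also, intent-to-treat including dropouts is planned, and a ranking rule may stand in a fuller document. A reader might infer that completers are the designated primary population. The text does not support that: the order and wording put them first, but the endpoint and model sentences attach no population. What remains is an order that is stated, not merely left out, and a fuller plan that made intent-to-treat decisive would have to turn this sentence round.

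Secondly, completer is not defined. It may mean finishing the modules or only having a post-treatment assessment. This stands, but both are settled after randomisation and both can differ by arm.

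Thirdly, a reader might infer that the completer result is certainly biased towards Deprexis. The documents do not show this. Early improvers may also stop, and worsening waitlist patients may leave for other care. The larger figures need a five-fold dropout gap related to outcome; with equal dropout and the same selection in both arms the bias vanishes. Nor does the Background help: its remark on "superiority of guided versus unguided self-help, both in terms of efficacy and drop-out rates" gives no rate by arm, and since this program is guided it would, if anything, suggest lower dropout.

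Finally, changing a label alone would not remove the bias. That is correct (step 5), and it is why the fix includes collecting the outcome.

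**Conclusion.** The point holds in a limited form. The article puts a post-randomisation subset first, adds the randomised comparison, and lets neither govern the 10-week endpoint. Intent-to-treat is demoted, not absent.

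The possible bias is about 0 with equal dropout, 0.03–0.10 SD with modest gaps, and 0.13–0.19 SD at 25% versus 5%. In that last case false positives in favour of Deprexis occur in 11–19% of trials instead of 2.5%. These sizes rest on an assumed r of 0.6, assumed dropout fractions and an assumed link between dropout and poor outcome. The direction rests on poor responders leaving the treated arm more often. The calculations show what the present wording exposes the trial to; they do not predict its result.

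**What to change.** State in the Statistical analyses section that:
- the primary analysis of the BDI-II at 10 weeks is intent-to-treat, in all randomised patients by assigned arm;
- the post-treatment assessment (T2) is sought from everyone, whatever their module use and even if they stop the program, unless they withdraw from the study;
- this result decides the conclusion;
- the completer analysis, with completer defined, is a supportive sensitivity analysis.

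Both analyses are already planned and the 80 randomised patients remain the denominator, so the cost is a few sentences plus some effort to obtain T2 from patients who stop. The price is a probably smaller headline effect.

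### The post assessment is anchored to 10 sessions in one sentence and to 10 weeks in the next; the session anchor cannot apply to the waitlist and leaves the midterm time undefined for controls

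*Protocol article*

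**What the plan says.** The Statistical analyses section of the protocol article plans a baseline-adjusted ANOVA whose outcome values come from "additional assessments conducted after 5 sessions (midterm) and after 10 sessions (post". Its next sentence reads: "The primary endpoint will be depressive symptoms measured by BDI II and a diagnostic interview after 10 weeks".

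Other sections bear on the timing:

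- **Assessment:** "The efficacy of the intervention is assessed post-treatment (T2) and additionally at 6 months follow-up (T3". For the midterm it says "depression levels are measured during treatment (T1), and treatment satisfaction is measured at the end of the treatment (T2". No week is given for T1 or T2.
- **Design:** "Patients under the waitlist condition receive the equivalent access to the program after a waiting period of 10 weeks".
- **Intervention:** "The treatment consists of 10 content modules". On their length it says "All modules can each be completed in 10 to 60 minutes", with the time varying from user to user. Feedback from the psychologist is weekly; no pace is set for the modules.
- **Statistical analyses, on patient sets:** a completer analysis, with an intent-to-treat analysis in addition that includes dropouts from the intervention or the waiting period. Missing values are to be estimated with an algorithm in SPSS.
- **Discussion:** because the waitlist gains access after ten weeks, the groups cannot be compared at six months.

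**The concern.** A number of sessions is a behavioural milestone; a number of weeks is a date. The two sentences give one of each for the same post measurement, and only the date can be used in the control arm.

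The post comparison is also the last randomised contrast in the trial, since the Discussion rules out a group comparison at six months. If staff schedule the treated arm by sessions, fast users are measured early and slow users late, and those who never reach a tenth session have no post value. Waitlist patients would all be due at week 10. Timing and availability of the outcome would then depend on something that happens after randomisation, in one arm only. The midterm value has the same problem without a calendar sentence to fall back on, although it enters the same efficacy model.

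**Working it through.** **1. Which arm can use which anchor**

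| Assessment | Session anchor | Calendar anchor | Usable in the waitlist? |
|---|---|---|---|
| Midterm (T1) | after 5 sessions | none stated | no: no sessions before week 10 |
| Post (T2) | after 10 sessions | 10 weeks | calendar only |

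**2. Do the two anchors coincide?** For the post value they coincide for a given patient only if the tenth session falls at week 10. The article gives 10 modules, a length that varies by user, and weekly feedback. It sets no rule of one module per week and never equates a session with a module. Agreement is possible but not secured by the text.

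**3. Is there a stated figure to reproduce?** The timing point has none. The sample size of 40 per arm does not depend on it, but it supplies a scale. The article says only that the effect is medium and gives no pre-post correlation. Assuming d = 0.5 and r = 0.60, the ANCOVA residual SD is √(1 − 0.60²) = 0.80. That needs 41 per arm (82 in total) for 80% power, and 40 per arm gives 79.8%. The stated size is attainable, and these two values are used below.

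**4. Hypothetical size if the session anchor were followed.** Suppose only treated patients who finish have a post value, all 40 waitlist patients are measured, and observed cases are analysed. Completion rates and correlations are assumptions; the article gives none.

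*Loss of power* (d = 0.5, r = 0.60, selection ignored):

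| Treated patients finishing | n treated | Power |
|---|---|---|
| 100% | 40 | 79.8% |
| 80% | 32 | 75.0% |
| 60% | 24 | 67.7% |
| 50% | 20 | 62.6% |

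*Bias with no true effect.* Let q be the fraction not finishing and ρ the correlation between finishing propensity and residual improvement. For a normal propensity cut at its q-quantile z:

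bias = ρ × √(1 − r²) × φ(z)/(1 − q)

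- q = 0.30, ρ = 0.3: φ(z) = 0.3477, so 0.3 × 0.80 × 0.3477/0.70 = 0.119 SD. The standard error is 0.80 × √(1/28 + 1/40) = 0.197, and a nominal 5% test rejects about 9.3%.
- q = 0.40, ρ = 0.4: φ(z) = 0.3863, so 0.4 × 0.80 × 0.3863/0.60 = 0.206 SD. The standard error is 0.80 × √(1/24 + 1/40) = 0.207, and the test rejects about 17%.

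Simulation of the same set-up (4,000 trials per setting) gives 0.117 SD with 9.2% rejection, and 0.203 SD with 16.4%, so formula and simulation agree.

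*Simpler range.* If finishers and non-finishers differ by 0.25 SD, the treated mean shifts by (1 − completion) × 0.25. That is 0.05 SD at 80% completion and 0.125 SD at 50%, or 10% and 25% of d = 0.5.

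**The case against.** A reader might infer that the arms will be measured at different times and on differently selected patients, and that the randomised comparison is therefore broken. The article does not support that. The sentence defining the primary endpoint gives 10 weeks without splitting by arm, and the waiting period is also 10 weeks. Read literally, both arms have the primary outcome at week 10. The session wording does not say that a questionnaire is withheld from anyone with fewer sessions, and it may be shorthand for the middle and end of a ten-week course. Reading sessions as completed modules is plausible, because there are ten modules, but it is an inference.

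The planned intent-to-treat analysis with missing-value estimation also counts against the claim that non-adherent patients leave the primary outcome. The hypothetical figures above do not assess that analysis, and they remove patients from the treated arm only, although the article expects dropout during the waiting period too. Any shift from timing alone has no settled direction, since early and late measurements partly offset each other. A completer analysis excludes dropouts whatever the anchor.

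All of this stands and limits the point to a conditional one. It does not remove the conflict. The objection that an article leaves visit windows to the full protocol does not answer it either: this is not missing detail but two stated timings, one of which cannot be used in the control arm. Intent-to-treat would not fully rescue a session trigger, because non-finishers would then have no observed post value and the estimation step would have to supply it.

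**Conclusion.** The concern holds as a conflict between two stated rules. The post outcome has a session anchor and a week anchor, the session anchor is impossible for the waitlist, and T1 has no defined time for controls.

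The consequence depends on which rule is applied. Under the 10-week sentence the primary endpoint is unaffected and only T1 remains open. Under the session wording, the time and availability of the post value would follow adherence in one arm, which could bias the comparison, most directly in the completer analysis.

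The bias of roughly 0.12 to 0.20 SD and the rejection rates of about 9% to 16% are hypothetical. They rest on assumed non-completion of 30% to 40%, correlations of 0.3 to 0.4, r = 0.60, one-sided loss and observed cases. They show why the wording is worth settling; they are not an estimate for this trial.

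**What to change.** Replace the session wording in Statistical analyses with calendar times: T1 at week 5 and T2 at week 10 after randomisation, in both arms, collected from every randomised patient regardless of sessions completed. Use the same definitions in the Assessment section. Report the number of sessions completed as an adherence variable, and state whether a session means a module.

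The cost is about one sentence, plus scheduling the online questionnaires by date. The statistical price is that some treated patients will be assessed before finishing the program, so the estimated effect may be slightly smaller. Recruitment is described as ongoing, and a week-10 value not collected on time cannot be recovered later, so the change is best made promptly.
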